### Sample size

The sample size is calculated using the statistical test for proportions based on the hypothesis that combination therapy using praziquantel plus an artemisinin-based combination is not inferior to praziquantel alone in treating schistosomiasis. Assuming a cure rate of 72% with praziquantel based on longitudinal studies from western Kenya [29], a cure rate of 62% (maximum difference of 10%) is considered clinically acceptable for non-inferiority of praziquantel plus an ACT combination therapy. With this non-inferiority margin, a power of 80%, and a one-sided alpha value of 0.025, a sample size of 102 children is needed in each treatment arm. To account for a 5% loss to follow-up, the total number of children to be enrolled and randomized is 540 (108 in each study arm).

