### Outcomes

The primary efficacy outcomes are as follows:Cure rate at week 6 after starting study treatments, as assessed by microscopy. The cure rate on each PZQ plus ACT arm is compared with that on the PZQ alone arm.The number of participants with drug-related adverse events in the first 24 h after study treatment.

The secondary outcomes are as follows:Cumulative cure rate at week 12 after enrollment, as assessed by microscopy. The cure rate on each PZQ plus ACT arm is compared with that on the PZQ alone arm.Egg reduction rate at weeks 6 and 12 after starting treatment, as assessed by microscopy and intensity reduction rate, comparing each PZQ plus ACT with PZQ alone arm.The prevalence of re-infection at 12 after starting treatment, as assessed as the number of children who were cured at week 6 follow-up but positive for *S. mansoni* at the week 12 follow-up, compared each PZQ plus ACT arms to the PZQ alone arm.

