### Data management and analysis

Data collected from each participant is recorded on paper-based case report forms (CRFs) in black ballpoint pen. The principal investigator will ensure that the data in the CRFs are accurate, complete, and legible. Data from the case record forms is entered by a data clerk into computers as they accrue using the MS Access program. The data is verified by comparing it with the CRFs. Missing data is imputed as either treatment success or treatment failure (assuming the same infection intensities before and after treatment). Validated data is transferred to SPSS version 20 and STATA version 12 for statistical analyses. The CRFs and the electronic data will be kept for 5 years after the primary manuscripts are published.

Data is analyzed using SPSS for Windows version 20 (SPSS Inc., Chicago, IL) and STATA version 12.0 (StataCorp., College Station, TX, USA) packages. A two-sided *p*-value less than 0.05 is considered statistically significant for all tests.

Demographic and other baseline characteristics are compared to check for imbalances between the study groups. These measures will be tabulated from the intent-to-treat population. Significance tests are not performed to compare the differences between study groups at baseline. Where imbalances are suspected, additional analyses are performed to adjust for these variables.

To determine efficacy, both the per-protocol and intention-to-treat analyses are done, but the per-protocol analysis is the main approach. The primary efficacy outcome is the cure rate, defined as the proportion of children infected with *S. mansoni* at enrollment but not excreting eggs by week 6 after taking the study treatment. In the computation of the cure rate, children randomized to the PZQ alone study arm are considered the control group. Cure rates are compared between the treatment groups using Pearson’s chi-square test for contingency tables (in a per-protocol analysis) and summarized as absolute risk differences with 95% confidence intervals (CI). The per-protocol population is defined to include all participants who were randomized and who completed the study procedures to week 6 or 12. The primary hypothesis for non-inferiority is assessed by considering the lower limit of the 95% CI for the risk difference. Non-inferiority is concluded if the lower bound of the 95%CI from the risk difference does not exceed the non-inferiority margin of − 10.

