The cumulative cure rate at week 12 is assessed by calculating a two-sided difference in proportions of cured children from each PZQ plus ACT arm compared with the PZQ alone arm. Arithmetic mean (AM) egg counts are computed for all non-cured participants. The egg reduction rate is computed as (1 − (AM EPG after treatment/AM EPG before treatment)) × 100. The ERR is expressed as a percentage. Re-infection rate is the proportion of children who test negative for *S. mansoni* at week 6 but test positive at week 12 follow-up. Changes in continuous variables over time are assessed using analysis of variance (ANOVA). The least significant difference will be used to assess post hoc pair-wise comparisons between the group means. Logistic regression will be used for analyses adjusted for the treatment received.

For the primary safety analysis, the frequency and pattern of adverse events are computed by patient counts and percentages in each of the five treatment groups. Adverse events are computed for all participants who received at least one dose of the study drug (intention-to-treat population).

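### Re-infection is defined once as a count and once as a proportion with no stated denominator; both depend on the week-6 result, and with no true effect the two can point in opposite directions

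*Protocol article*

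**What the plan says.** Re-infection at 12 weeks is a secondary objective, and the protocol article defines it in two places.

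- **Outcomes:** it is called a prevalence but is "as assessed as the number of children who were cured at week 6 follow-up but positive for" *S. mansoni* at week 12, "compared each PZQ plus ACT arms to the PZQ alone arm". This is a count with a between-arm comparison.
- **Data management and analysis:** "Re-infection rate is the proportion of children who test negative for" *S. mansoni* "at week 6 but test positive at week 12 follow-up". This is a proportion whose denominator is not named.

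Both versions start from the week-6 stool result. That result is also the primary efficacy outcome: a child is cured if infected at enrolment "but not excreting eggs by week 6 after taking the study treatment". It rests on duplicate slides from one stool sample, read independently by two technicians (Parasitological monitoring of response to treatment).

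A neighbouring secondary outcome is handled separately: "The cumulative cure rate at week 12 is assessed by calculating a two-sided difference in proportions of cured children" between each combination arm and praziquantel alone. Neither section says whether a child who is negative at week 6 and positive at week 12 counts as cumulatively cured.

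**The concern.** Treatment is expected to change the week-6 result, so a re-infection measure built on that result is affected in three ways.

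1. **Count.** A child still positive at week 6 can never be counted as re-infected. At equal re-infection risk, the arm that cures more children has more of them at risk and a higher count.
2. **Proportion among week-6 negatives.** Children who clear infection on praziquantel alone may differ in exposure from those who clear it on a combination. The groups compared are then selected by response, not by randomisation.
3. **Missed infections.** A residual infection missed at week 6 and found at week 12 is recorded as re-infection. The arm with more true failures has more of these.

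The Introduction motivates the combinations partly by praziquantel's failure to prevent re-infection, and the Discussion looks ahead to transmission control and chemoprophylaxis. Re-infection is the secondary outcome closest to those claims. The data analysts are not blinded, so leaving two measures open also leaves room for a choice made after seeing the data.

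**Working it through.** The article gives no expected rate, power or sample size for re-infection, so there is no figure to reproduce.

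**Inputs from the article (Sample size):** "Assuming a cure rate of 72% with praziquantel"; "a sample size of 102 children is needed in each treatment arm".

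**Assumptions, not in the article:** combination cure rate (86% or 90%); re-infection risk between weeks 6 and 12 (0%, 10%, 20%, or 5%/25% by stratum), with no treatment effect on it; stool sensitivity Se per visit (0.6 to 0.9), equal at both visits and independent between them; specificity 100%.

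**A. Count, perfect test, equal risk.** Count = n × cure × risk. At 10% risk:
- 72% cure: 102 × 0.72 × 0.10 = 7.3
- 86% cure: 102 × 0.86 × 0.10 = 8.8

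The ratio between arms is the ratio of cure rates, 0.86/0.72 = 1.19, whatever the risk. The more curative arm looks worse.

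**B. Proportion among week-6 negatives, zero true re-infection.** Let c be the observed week-6 cure rate. True failures are (1 − c)/Se. Those missed at week 6 and found at week 12 are (1 − c)/Se × (1 − Se) × Se. Dividing by c gives

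apparent re-infection = (1 − c)(1 − Se)/c.

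| Se | c = 0.72 | c = 0.86 | Difference (points) |
|---|---|---|---|
| 0.6 | 15.6% | 6.5% | 9.0 |
| 0.7 | 11.7% | 4.9% | 6.8 |
| 0.8 | 7.8% | 3.3% | 4.5 |
| 0.9 | 3.9% | 1.6% | 2.3 |

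(Differences are taken before rounding.) The more curative arm looks better although nobody was re-infected.

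**C. Selection alone, perfect test.** Half the children have 5% risk and half 25%, the same in both arms. Cure is 90%/54% on praziquantel (72% overall) and 92%/88% on the combination (90% overall).
- Praziquantel: (0.5 × 0.90 × 0.05 + 0.5 × 0.54 × 0.25)/0.72 = 0.090/0.72 = 12.5%
- Combination: (0.5 × 0.92 × 0.05 + 0.5 × 0.88 × 0.25)/0.90 = 0.133/0.90 = 14.8%

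Here the same proportion makes the more curative arm look worse.

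**D. Both measures on the same children.** True cure 72% versus 90%, equal 20% risk, Se = 0.9.
- Negative at week 6, positive at week 12: 0.72 × 0.20 × 0.9 + 0.28 × 0.1 × 0.9 = 0.1548 for praziquantel; 0.90 × 0.20 × 0.9 + 0.10 × 0.1 × 0.9 = 0.1710 for the combination.
- Negative at week 6: 0.72 + 0.28 × 0.1 = 0.748 and 0.90 + 0.10 × 0.1 = 0.910.
- Count per 102: **15.8 versus 17.4**, in favour of praziquantel alone.
- Proportion of week-6 negatives: 0.1548/0.748 = **20.7%** versus 0.1710/0.910 = **18.8%**, in favour of the combination.

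The truth in this case is no difference in re-infection risk.

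**The case against.** A good deal can be said for the plan, and part of it stands.

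- **A reader might infer that the whole re-infection comparison is no longer randomised.** The documents do not support that. A count per arm under equal allocation still compares the randomised groups; its fault is that it does not measure re-infection risk. Loss of randomisation applies only to the proportion, and only if the denominator is week-6 negatives. That reading is natural but not stated. A joint proportion over all children in an arm is also possible; it keeps the randomised groups but, like the count, moves with the cure rate.
- **The count may be loose wording.** The Outcomes section calls the measure a prevalence and uses similar wording for adverse events, which are analysed as counts and percentages. This is fair, but it leaves the denominator open.
- **The sizes rest on assumptions.** This stands. Zero re-infection is an extreme case in an area with prevalence up to 75%. At Se = 0.6, an observed cure of 72% implies a true cure of only 1 − 0.28/0.6 = 53%. Residual light infections may also be missed repeatedly, which breaks independence between visits.
- **The bias is small against sampling error.** With 102 × 0.72 = 73 and 102 × 0.86 = 88 week-6 negatives, the differences in table B are 1.8, 1.5, 1.2 and 0.9 standard errors. None reaches 1.96 by itself. A shift of that size still matters: under a normal approximation, the chance of a two-sided p below 0.05 is about 44% at 1.8 standard errors and about 14% at 0.9, not 5%.
- **The objective is only to assess the rate, and week-12 cumulative cure is already compared.** No hypothesis is attached to re-infection, but the Outcomes section does compare it between arms. Cumulative cure does not repair that comparison.
- **Egg-negative at both visits is a different question.** This stands. It mixes treatment failure with re-infection, so it can be added but cannot replace the stated objective.

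**Conclusion.** The concern holds in a limited form. One secondary outcome has two definitions. One rises with the cure rate by construction. The other leaves its denominator open and, on its natural reading, conditions on a post-treatment result that also contains missed infections. Followed as written, either can give a misleading between-arm result, and the two can disagree on the same data.

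The illustrative size is a spurious benefit of about 9.0 to 2.3 points for the combination. It assumes zero true re-infection, 72% versus 86% observed cure, specificity of 100%, and equal, independent sensitivity of 0.6 to 0.9. The mechanisms do not need these exact values. The net direction does: selection can push the proportion the other way, so it would be wrong to say that the plan is biased for or against the combinations overall.

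The primary non-inferiority conclusion at week 6 is unaffected.

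**What to change.** 1. Use one definition in both sections: among children egg-negative at week 6 who have a week-12 stool, the proportion positive at week 12. Give numerator and denominator by arm.
2. Read the between-arm contrast of this proportion descriptively, and state that week-12 positives may include residual infections missed at week 6.
3. Add a between-arm comparison over all randomised children (108 per arm) of the proportion egg-negative at both week 6 and week 12, as a risk difference with 95% CI. Label it sustained clearance, not re-infection, and say how a child with a missing stool at either visit is counted.
4. State whether cumulative cure at week 12 means this same quantity, so that no child is counted as both cured and re-infected.

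**Cost.** Revised wording and one extra table, from stools already scheduled. The causal claim about re-infection becomes more modest. The trial is open-label, the analysts are unblinded and recruitment is complete, so this is a late change to secondary outcomes. It should be documented and dated before the analysis, and the article says that protocol changes go to the ethics committee for approval.

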### Study design

The SCHISTOACT study is designed as a phase III, open-label, five-arm, head-to-head, proof-of-concept, individually randomized, controlled, non-inferiority trial. The participants are randomly allocated (ratio 1:1:1:1:1) individually to one of five treatment groups. At baseline, participants in the control arm receive praziquantel (PZQ, single dose of 40 mg/kg). Those in the intervention arms receive a single dose of praziquantel (40 mg/kg) plus a 3-day course of one of four artemisinin-based combination therapies (4 mg/kg of the artemisinin component, once a day for three consecutive days, as fixed-dose WHO-recommended combination treatment for uncomplicated falciparum malaria). The four artemisinin-based combination therapies (ACTs) that are combined with praziquantel are artesunate plus sulfalene/pyrimethamine, artesunate plus amodiaquine, artesunate plus mefloquine, and dihydroartemisinin-piperaquine. These four ACTs were selected because they are widely available for malaria treatment, co-formulated, for once-daily dosing therapy, have a well-established safety profile and have all been evaluated for treating schistosomiasis with inconclusive results. The 6-week interval between the administration of study treatment and evaluation of primary endpoints has been chosen because it corresponds to the duration of schistosome larval maturation. The participants will be followed up at 6 and 12 weeks. During these follow-up visits, stool samples will be collected, and clinical assessments will be performed. All children will receive a standard dose of praziquantel at the end of the study. The study flow chart is shown in Fig. 1.

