#### Parasitological monitoring of response to treatment

All the laboratory tests are performed by the laboratory at the sub-county hospital, using standard techniques. To assess for the presence of *S. mansoni*, participants provided a fresh stool sample. Duplicate slides are prepared from the stool sample and examined under the microscope independently by two experienced laboratory technicians. The *S. mansoni* and soil-transmitted helminth eggs are quantified by use of the Kato-Katz fecal thick-smear technique, with a template containing about 41.7 mg of feces when filled. The number of *S. mansoni* eggs is counted per slide, and the mean of the two readings is multiplied by 24 to express them as eggs per gram (EPG) of feces. The intensity of infection is categorized according to the WHO classification as light (1–99 EPG), moderate (100–399 EPG), or heavy (≥ 400 EPG) [30]. As a quality control measure for interobserver variability, a third technician reads a random selection of 10% of slides, and all slides for which the initial readings vary by more than 20% between the two technicians.

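### The re-infection rule counts an infection missed at week 6 and found at week 12 as new, so part of the reported rate, and of any difference between arms, can be missed residual infection

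*Protocol article*

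**What the plan says.** The rule appears in two places in the protocol article. The Outcomes section describes re-infection as "the number of children who were cured at week 6 follow-up but positive for" S. mansoni at week 12, "compared each PZQ plus ACT arms to the PZQ alone arm". The Data management and analysis section says: "Re-infection rate is the proportion of children who test negative for" S. mansoni "at week 6 but test positive at week 12 follow-up". One wording is a count and the other a proportion, and the denominator is not explicit.

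Cure is defined by the test alone, as "not excreting eggs by week 6 after taking the study treatment". Under Screening, enrollment, and participant follow-up, each child gives one stool at week 6 and one at week 12. On the reading of that stool, Parasitological monitoring says: "Duplicate slides are prepared from the stool sample and examined under the microscope independently by two experienced laboratory technicians". Quality control there is a third reading of some slides; the stool is not resampled. On retreatment, Study design says: "All children will receive a standard dose of praziquantel at the end of the study". No study praziquantel is therefore scheduled between the two visits.

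**The concern.** A child who is still infected but sheds few eggs can show none on both slides at week 6 and some at week 12. Followed exactly, the rule scores that child first as cured and then as re-infected, although nothing new was acquired. Re-reading slides catches reader error but cannot find eggs that were not in the sampled stool. The rule also uses only one direction of disagreement: children positive at week 6 and negative at week 12 carry information on how often infection is missed, and they are not used.

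The number of such false re-infections depends on how many children remain uncured, so the comparison between arms mixes treatment failure with new infection. An ACT combination that only clears more existing infection could appear to protect against re-infection. This matters because the Introduction and Discussion argue that adding an ACT may block transmission, and re-infection is the listed outcome closest to that claim.

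**Working it through.** The protocol states no re-infection rate and no test sensitivity, so it has no figure of its own to reproduce.

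**Inputs.** From Sample size: 72% cure on praziquantel, 62% as the lowest acceptable cure on a combination, 102 children per arm. From Parasitological monitoring: two slides of about 41.7 mg, mean count multiplied by 24. Assumed: per-visit sensitivity *s* of 50% to 90%, equal at both visits; independent visits; no false positives; 85% cure for a better arm.

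**1. Can residual infection be missed?** One egg on one slide and none on the other is 0.5 × 24 = 12 EPG. The two slides hold 83.4 mg, so a true 12 EPG gives an expected 0.0834 × 12 = 1.0 egg. If eggs were evenly mixed (Poisson), both slides would be empty with probability exp(−1.0) = 37%. At 24 EPG it is exp(−2.0) = 14%. The implied sensitivities, 63% and 86%, fall inside the assumed range.

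**2. No transmission.** Let *c* be the observed share negative at week 6.
- Truly uncured: u = (1 − c)/s
- Missed at week 6 and found at week 12: u(1 − s)s = (1 − c)(1 − s)
- As a share of week-6 negatives: (1 − c)(1 − s)/c

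| s | c = 62% | c = 72% |
|---|---|---|
| 90% | 6.1% | 3.9% |
| 80% | 12.3% | 7.8% |
| 70% | 18.4% | 11.7% |
| 60% | 24.5% | 15.6% |
| 50% | 30.6% | 19.4% |

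For example, 0.28 × 0.3/0.72 = 11.7%. In an arm of 102 with 72% cure (about 73 week-6 negatives), the range is 102 × 0.28 × 0.1 = 3 to 102 × 0.28 × 0.5 = 14 children.

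**3. Other readings at 72%.**
- All children as denominator: 2.8% to 14.0%
- 72% taken as the true cure rate: 3.4% to 8.1%
- Detection varying strongly between children (Beta distribution, parameters summing to 2): 2.6% to 13.0%
- Sensitivity of 95%: 1.9%

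**4. Between arms, no transmission.** At s = 70% in every arm: 18.4% at 62% cure, 11.7% at 72%, and 0.15 × 0.3/0.85 = 5.3% at 85%. With unequal sensitivity the order can reverse: 72% cure at s = 80% gives 7.8%, while 85% cure at s = 50% gives 0.15 × 0.5/0.85 = 8.8%.

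**5. With transmission.** Let *L* be the chance that a truly cured child becomes detectably infected between the visits, the same in both arms. Take s = 70% and L = 20%.
- 72% cure: u = 0.28/0.7 = 0.40. Missed then found = 0.28 × 0.3 = 0.084; new and found = 0.60 × 0.2 × 0.7 = 0.084. Current rule: 0.168/0.72 = 23.3%.
- 85% cure: u = 0.15/0.7 = 0.214. Missed then found = 0.045; new and found = 0.786 × 0.2 × 0.7 = 0.110. Current rule: 0.155/0.85 = 18.2%.

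Positive-to-negative children make up u·s(1 − s), which equals the missed-then-found share. Subtracting them leaves 0.084/0.72 = 11.7% against 0.110/0.85 = 12.9%. Divided by all children instead, the net figures are 8.4% against 11.0%.

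In general, the gap between arms with cure rates c₁ and c₂ is (1 − L)(1 − s)(1/c₁ − 1/c₂) under the current rule. For the net measure over week-6 negatives it is L(1 − s)(1/c₁ − 1/c₂), in the opposite direction. The net measure therefore has the smaller bias whenever L is below 50%.

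**The case against.** A reader might infer that the rule will report 4% to 19% re-infection even without transmission. The documents do not support that as a statement of fact. They give no sensitivity, and the range also needs independent visits, 72% read as observed cure, and week-6 negatives as denominator. Its upper end implies that 0.28/0.5 = 56% of praziquantel children are truly uncured. The figure stands only as an illustration.

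A reader might also infer that a lower-cure arm always shows more false re-infection. That holds only at equal sensitivity. An arm with lower residual egg counts could have lower sensitivity, and step 4 shows the order reversing.

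Nor is the net change a clean measure of re-infection. Positive-to-negative children may include late clearance or outside treatment, and the withdrawal criteria anticipate self-medication. The measure can be negative. Divided by all children, it is pulled by the cure rate as soon as there is transmission, and the study area is endemic. These points stand, and they are why it serves as a sensitivity comparison over week-6 negatives and not as a replacement outcome.

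Finally, re-infection is a secondary outcome, the non-inferiority conclusion rests on week-6 cure, and an unseen analysis plan may add sensitivity analyses. That limits the weight of the point but does not answer it: the article itself fixes the rule and the comparison, and the rule misclassifies when followed exactly.

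**Conclusion.** The concern holds in a limited form. The stated rule counts infections missed at week 6 and found at week 12 as new, and nothing in the protocol separates the two. The artefact is above zero whenever some uncured children are missed at week 6 and found later. Under the no-transmission illustration it is 3.9% to 19.4% of week-6 negatives at 72% observed cure, and roughly 2% to 14% on other readings. At equal sensitivity across arms it favours the arm with higher cure. At 70% sensitivity and no transmission, 85% against 72% cure would read 5.3% against 11.7%, a difference of 6.4 points unrelated to new infection. The size depends on an assumed sensitivity, and the direction on similar detectability across arms. The primary week-6 non-inferiority comparison is not affected by this rule.

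**What to change.** 1. Keep the negative-to-positive proportion, state its denominator as week-6 negatives with both stools, and label it 'new or previously missed infection'.
2. Report the positive-to-negative count in each arm beside it.
3. Add a sensitivity comparison of each ACT arm with praziquantel, with a 95% CI, using (negative-to-positive minus positive-to-negative) divided by week-6 negatives with both stools, not by all children.
4. Draw no conclusion of protection against re-infection unless both measures agree.

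Both stools are already collected, so the cost is one added derivation and a label. The net comparison has a wider interval. It assumes similar detectability at the two visits and no late clearance or outside treatment among positive-to-negative children. A small bias remains: at 70% sensitivity and 20% true risk in both arms, 11.7% against 12.9% for 72% against 85% cure, compared with 23.3% against 18.2% under the current rule. Because data analysts are not blinded, the change should be written down before week-12 results are compared by arm. If they have already been compared, it should be reported as post hoc.

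### The egg reduction rate is to be compared between arms, but the only method given for continuous variables, ANOVA on changes, would test absolute egg-count change if it were used for that comparison

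*Protocol article*

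**What the plan says.** The Outcomes section lists the egg reduction rate at weeks 6 and 12 as a secondary outcome, with "intensity reduction rate, comparing each PZQ plus ACT with PZQ alone arm". The Data management and analysis section then fixes four things:

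- The definition: "The egg reduction rate is computed as (1 − (AM EPG after treatment/AM EPG before treatment)) × 100".
- The children behind the means: "Arithmetic mean (AM) egg counts are computed for all non-cured participants".
- The method for continuous variables: "Changes in continuous variables over time are assessed using analysis of variance (ANOVA"), and after it "The least significant difference will be used to assess post hoc pair-wise comparisons between the group means".
- The threshold: a two-sided p-value "less than 0.05 is considered statistically significant for all tests".

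The other named methods have other uses: the chi-square test is for cure rates, and logistic regression is for adjusted analyses. No transformation, ratio-scale test or interval is given for ERR. The Sample size section gives "a power of 80%, and a one-sided alpha value of 0.025" for the cure rate only. It states no egg-count standard deviation, expected ERR or power for ERR.

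**The concern.** ERR is one number per arm, so no child has an ERR value that could enter an ANOVA. EPG is the only continuous quantity among the listed outcomes, and its arithmetic means are the only means the section names. An analyst following the text would therefore probably run ANOVA on each child's change in EPG.

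That analysis reports a difference in EPG, not in proportional reduction. When both arms lose most of their eggs, a child's change is nearly the child's baseline count. The comparison then carries the full spread of baseline intensity as noise. A real but modest gain in ERR would usually come out as not significant and could be reported as no benefit on egg reduction.

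**Working it through.** **Plan's own figure.** There is none for ERR. The 102 per arm comes from the cure-rate calculation and is used here only as the number of children.

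**Inputs from the article.** 102 per arm; two-sided 0.05; control cure rate from "Assuming a cure rate of 72% with praziquantel".

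**Inputs assumed.** Baseline EPG is gamma distributed with mean 100 to 300 and shape (dispersion) 0.5 to 1, with 0.25 as a more skewed case. Kato-Katz counting noise is added. The residual counts of uncured children vary between children. The combination arm cures 72% or 86%.

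**Step 1: signal against noise.** Express change as a fraction of the baseline mean. With equal expected baselines, a 5-point ERR difference shifts mean change by 0.05. The standard error of the difference in mean change is about CV × √(2/102), which is 0.14 at CV 1 and 0.28 at CV 2. The shift is well below one standard error.

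**Step 2: analytic power of the change test.** Power ≈ Φ(d/CV × √(102/2) − 1.96), counting significance in the right direction only, with d the ERR difference and the SD of change taken as CV × baseline mean.

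- d = 0.05, CV 1: Φ(0.357 − 1.96) = 0.05. At CV 2: 0.04.
- d = 0.10, CV 1: Φ(0.714 − 1.96) = 0.11. At CV 2: 0.05.
- d = 0.30, CV 1: Φ(2.142 − 1.96) = 0.57. At CV 2: 0.19.
- 80% power at d = 0.05 and CV 1 needs 2 × (1.96 + 0.842)² × (1/0.05)² ≈ 6,280 per arm.

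**Step 3: simulation.** Two arms of 102, mean baseline 200 EPG, 600 trials per row. The change test is a two-arm test on (before − after). The ratio test permutes children and compares after/before mean ratios. Entries are the percentage of trials significant.

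| Shape | ERR, control v combination | Cure | Change, all | Ratio, all | Change, non-cured | Ratio, non-cured |
|---|---|---|---|---|---|---|
| 0.5 | 90 v 90 | 72 v 72 | 6.5 | 4.0 | 3.8 | 5.3 |
| 0.5 | 90 v 95 | 72 v 86 | 4.7 | 24.8 | 4.5 | 4.5 |
| 0.5 | 90 v 97 | 72 v 86 | 5.7 | 43.0 | 9.3 | 5.3 |
| 0.5 | 60 v 90 | 72 v 86 | 24.5 | 56.0 | 12.8 | 11.2 |
| 1 | 90 v 90 | 72 v 72 | 5.2 | 4.2 | 4.7 | 4.8 |
| 1 | 90 v 95 | 72 v 86 | 6.0 | 25.0 | 5.2 | 4.7 |
| 1 | 90 v 97 | 72 v 86 | 7.3 | 56.7 | 8.2 | 8.5 |
| 1 | 60 v 90 | 72 v 86 | 33.2 | 66.8 | 16.0 | 16.7 |

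Under other assumptions:

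- At shape 0.25 with 72% cured in both arms, 90% v 95% gives 5.5% against 12.3%. This is the low end of the ratio test's range.
- With baseline means of 100 or 300 EPG and different residual-count assumptions, the ratio test reaches 61–72% for 90% v 97%, and the change test stays at or below 9%.
- In those runs the arm difference in mean change shared 91–95% of its variance with the chance difference in baseline means, and 2–12% with the observed ERR difference.
- For 60% v 90% the change test ranges from 14% to 46%.

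**Step 4: the non-cured restriction.** For overall ERR of 90% v 95% with cure of 72% v 86%, ERR among the uncured is 1 − 0.10/0.28 = 64% in control and 1 − 0.05/0.14 = 64% in the combination arm. The restriction removes the whole difference, so no test could find it. Across the tabulated model, about 7 to 25 children per arm remain with eggs. The change test then has 4–18% and the ratio test 4–31%, or up to 43% under other residual-count assumptions.

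**The case against.** The strongest objection is that the link is inferred. The ANOVA sentence names neither ERR nor egg counts, and two sentences separate it from the ERR formula. Hemoglobin, weight and height are measured at baseline, week 6 and week 12 and fit the sentence naturally. A condensed article may leave the ERR comparison to an analysis plan that is not shown. This stands as far as it goes: a reader might infer that the protocol prescribes ANOVA for ERR, and it does not say so. But the article does state a method for continuous variables, and none of those other measurements is a listed outcome. Following the text still leads to EPG change.

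Three further inferences are tempting and not supported:

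- **That ANOVA has almost no power for ERR in general.** This holds for modest gaps at high ERR under assumed inputs, and not for 60% v 90%. High ERR is the more plausible range if 72% are cured: with cure unrelated to baseline intensity and no rise in uncured children, overall ERR is at least 72%.
- **That false positives are inflated.** Randomization gives the arms equal expected baselines, so equal ERR implies equal expected change. Rejection under equal rates stayed at about 3–7%. The loss is in power and in the quantity reported.
- **That a new test alone would restore power.** Step 4 shows otherwise if the means stay restricted to non-cured children.

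The article's provision to adjust for suspected baseline imbalance helps in part, but it is conditional and does not put the comparison on the ratio scale.

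**Conclusion.** The point holds in a limited form. The article promises an ERR comparison, defines ERR as a ratio of means, and states no method that compares that ratio between arms. Its one method for continuous variables, if applied to raw egg counts, answers a question about absolute EPG change. For the modest differences that are plausible at high ERR, its power is close to the significance level, and a ratio-scale test on all children does clearly better, though still often below 80%. For large gaps the change test is weak but not empty.

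Every power figure rests on assumed baseline skewness, residual counts and ERRs, because the article gives none. The non-cured results are especially sensitive to how much residual counts vary between uncured children. The outcome is secondary, so this should be changed but does not threaten the primary analysis.

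**What to change.** State in the analysis section that:

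- ERR at weeks 6 and 12 is computed on all assessed children in each arm, with cured children counted as zero EPG.
- Each combination arm is compared with praziquantel by the ratio of (mean EPG after / mean EPG before), with a 95% bootstrap interval resampling children within arm, or a permutation test. Resampling is preferable to a delta-method test of the log ratio, whose type I error was 0.06–0.11 in simulation. A negative binomial model of the follow-up count with log link, arm and log baseline EPG would also serve.
- ANOVA on changes applies to hemoglobin and anthropometry only.

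The cost is a few sentences and a short script or one regression command. No new data are needed. The small downside is a method less familiar than ANOVA.
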